## Abstract

**Background:**

Cancer is the leading cause of death in Canada, responsible for 28.2% of all deaths. Based on surgical candidacy and disease status, both lung and esophageal cancer are treated through surgical resection by a thoracic surgeon. Although surgery contributes to improved outcomes, the 30-day postoperative mortality risks are as high as 10% and 2.8%, respectively. Evidence has shown that prehabilitation is a way in which patients can have improved postoperative outcomes. Prehabilitation is multimodal, often including some form of movement, nutrition, stress management, and smoking cessation. Given the complexity of the health care system, pragmatic trials are important methodological tools to assess internal validity and improve current practice under real-world conditions. Concurrently, using community resources is imperative to keep people active in their community and create sustainable programming.

**Objective:**

The Boosting Recovery and Activity Through Early Wellness (BREATHE WELL) study aims to explore the feasibility, implementation, and preliminary effectiveness of a clinically integrated, community-based, prehabilitation health coaching program. This includes nutrition, smoking cessation, sleep hygiene, and movement for individuals scheduled to undergo surgery for lung or esophageal cancer.

**Methods:**

This is a pilot, nonrandomized, pragmatic, repeated measures, mixed methods trial. We will recruit 32 participants diagnosed with lung or esophageal cancer and are scheduled to undergo surgical resection into the prehabilitation program, with 32 additional participants who decline participation to act as a control group. Participants who agree will then go through an 8-week tailored prehabilitation program (in person or virtual), covering movement, nutrition, stress management, nutrition, goal setting, and smoking cessation. They will complete 6 sessions prior to surgery and then have 4 sessions, 1×/week following surgery. Following the completion of the program, they will have 3 booster sessions via phone or Zoom (Zoom Video Communications). The primary outcome is feasibility: (1) recruitment feasibility—recruitment rate (the number of participants referred per month), enrollment rate (the number of enrolled participants divided by the number of referred participants), reasons for declining, and prehabilitation window (time between consent and surgery); and (2) intervention feasibility—adherence to the movement intervention, attrition, safety, study completion rate, and adverse events. Secondary outcomes include measures of preliminary effectiveness including patient-reported outcomes, such as well-being, fatigue, and functional measures. All measures will be assessed before, during, and after the prehabilitation program.

**Results:**

Enrollment has begun in January 2025, with 2 participants enrolled in the health coaching program. The full study is expected to be completed in approximately 3 years and be published in winter 2027.

**Conclusions:**

This study will inform the feasibility, implementation, and preliminary effectiveness of a clinically integrated, community-based, prehabilitation program in Nova Scotia, Canada, for people scheduled to undergo curative intent surgery for lung and esophageal cancer.

**Trial Registration:**

ClinicalTrials.gov NCT06354959; https://clinicaltrials.gov/study/NCT06354959

**International Registered Report Identifier (IRRID):**

PRR1-10.2196/60791

## Introduction

Cancer is the leading cause of death in Canada, responsible for 28.2% of all deaths [1]. Among these cancers, lung cancer is the most frequently diagnosed in the country, resulting in 25% of cancer-related deaths [2]. Esophageal cancer, while less common, presents unique challenges due to its effect on patients’ nutritional status, its tendency to metastasize rapidly, and, consequently, its poorer prognosis [3]. Based on surgical candidacy and disease stage, surgical resection by a thoracic surgeon is a mainstay of treatment for lung and esophageal cancers. Although surgery contributes to improved outcomes, the 30-day postoperative mortality risk are as high as 10% and 2.8% for lung and esophageal cancers, respectively [4,5]. Postoperative complications (eg, pneumonia and pain) pose a significant risk to patients undergoing curative-intent, lung and esophageal cancer surgeries [6]. These events not only increase the length of hospital stay but also negatively impact the patient experience, decrease quality of life, and result in substantial financial burdens for health care [7-10]. Therefore, it has been proposed that completing a prehabilitation program prior to undergoing surgery may lead to improved postoperative outcomes for patients. Prehabilitation refers to assessments and interventions initiated prior to treatment to create a physiological and psychosocial buffer against anticipated deconditioning, complications, and other comorbidities that typically occur as a result of treatment [11,12]. Prehabilitation is multimodal, often including some form of movement, nutrition, stress management, and smoking cessation.

Previous research has found that older adults (aged 70 years and older; American Society of Anesthesiologist score III/IV) who participated in prehabilitation experienced 50% less postoperative complications relative to the control group; this type of intervention was safe and feasible and showed cost-savings of up to €800 (~US $833.62) per patient [13]. Although prehabilitation interventions have generally shown benefit [14], there is still little uptake into the standard of care. This could be due to a wide variety of factors, including the complexity of implementing programs in a health care setting. Therefore, there needs to be more consideration for clinical care pathways, delivery strategies, and infrastructure and personnel for the local uptake of these programs.

Given the complexity of the health care system, pragmatic trials are important methodological tools to assess internal validity and improve current practice under real-world conditions [15]. Concurrently, using community resources is imperative to keep people active in their community and create sustainable programming. Practice-based evidence is an emerging field that strives to ensure research is applicable to real-world settings [16,17]. Practice-based evidence is derived from implementation science research methods, which assess effective intervention in real-world settings and provide insights into the system’s capacity and preparatory needs for dissemination and scalability [18]. The purpose of Boosting Recovery and Activity Through Early Wellness (BREATHE WELL) is to explore the feasibility, implementation, and preliminary effectiveness of a clinically integrated, community-based prehabilitation health coaching program, including nutrition, smoking cessation, sleep hygiene, and movement for individuals scheduled to undergo surgery for lung or esophageal cancer. Central to our research endeavor is the driving question: “How can a clinically integrated, community-based prehabilitation program be successfully implemented in the community, and can it lead to improved functional outcomes in patients undergoing surgery for lung or esophageal cancer?” This overarching question provides the study with its core focus and serves as a guiding force throughout the research process. The aim of this study is to investigate the implementation, feasibility, and effectiveness of BREATHE WELL, a community-based prehabilitation health coaching program specially designed for individuals scheduled to undergo surgery to address lung or esophageal cancer.

## Methods

### Design

This is a pilot, nonrandomized, pragmatic, repeated measures, mixed methods trial to assess the feasibility, implementation, and effectiveness of a clinically integrated, community-based, multimodal prehabilitation program for patients with lung and esophageal cancers in an urban academic health center in Halifax, Nova Scotia, Canada. Participant flow throughout the study is presented in Figure 1. This study aligns with the TREND (Transparent Reporting of Evaluations of Nonrandomized Design) checklist (Multimedia Appendix 1) for nonrandomized trials [19].

**Figure 1 figure1:**
[figure not shown]
Participant flow.

### Participants

Based on a monthly surgical volume of 10 patients per month to the referring surgeon, assuming an enrollment rate of 25% while accounting for 20% attrition within a 16-month recruitment window, we will seek to recruit 64 participants (aged 18 years and older) diagnosed with lung or esophageal cancer (32 in the program and 32 who decline). This is based on the number of surgical candidates that the current surgeon sees in a 2-year period. Participants will be identified based on the following inclusion criteria: (1) confirmed diagnosis of lung or esophageal cancer; (2) treatment plan includes surgery (at least 2 weeks from the time of consent) [20]; (3) fluent in English; and (4) surgical oncologist approval. Exclusion criteria include (1) unstable or symptomatic cardiac disease, musculoskeletal injury, or comorbid disease that precludes the ability to safely engage in physical activity or (2) significant cognitive limitations.

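### The program-group target of 32 is the number left after 20% attrition, but the protocol states it as the number to recruit; its own inputs give 40 to enrol

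*Protocol article*

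**What the plan says.** All the inputs stand in the Participants section of the protocol article. The starting figure is the caseload: "Based on a monthly surgical volume of 10 patients per month to the referring surgeon". The rates, the window and the target follow: "assuming an enrollment rate of 25% while accounting for 20% attrition within a 16-month recruitment window, we will seek to recruit 64 participants", split as "32 in the program and 32 who decline".

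The next sentence gives a further basis: "This is based on the number of surgical candidates that the current surgeon sees in a 2-year period".

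The Methods part of the abstract repeats the figure as a recruitment number: "We will recruit 32 participants diagnosed with lung or esophageal cancer", "with 32 additional participants who decline participation to act as a control group".

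The Enrollment and Assessment section makes non-participants the comparison group under a waiver of consent and sets no upper number. The second inclusion criterion requires surgery to be at least 2 weeks after consent. Outcome Measures sets feasibility targets of 25% for enrollment and 20% or less for attrition, the same two rates that enter the sample size.

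**The concern.** A target that accounts for attrition should exceed the number wanted at the end. Here the stated inputs lead to 32 only after attrition has been deducted, yet the text tells staff to recruit 32. Anyone following it would stop enrolling about a fifth short of what the inputs support and finish with fewer completers than the calculation produces.

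In a pilot whose primary outcome is feasibility, the enrolment target, the window, and the enrollment and attrition rates should agree, because the trial will be judged against those same rates. The target also sets the stopping point for enrolment.

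**Working it through.** **Inputs** (Participants section): 10 patients per month; 16 months; 25% enrollment; 20% attrition.

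**Reproducing the stated figure**

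- Candidates: 10 x 16 = 160
- Enrolled: 160 x 0.25 = 40
- Remaining after attrition: 40 x 0.80 = 32

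The stated 32 is reproduced exactly, but only at the last step. In the other direction, 32 / 0.80 = 40 must be enrolled to keep 32.

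**Check against the window**

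- Enrolment per month: 10 x 0.25 = 2.5
- Time to enrol 40: 40 / 2.5 = 16 months, which matches the stated window
- Time to enrol 32: 32 / 2.5 = 12.8 months, which does not

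**If 32 are recruited as written**

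- Completers: 32 x 0.80 = 25.6, about 26
- Confidence interval width for a mean change within the program group, relative to 32 completers: sqrt(32 / 25.6) = 1.12, so about 12% wider
- For a difference against 32 fully observed controls: sqrt[(1/25.6 + 1/32) / (1/32 + 1/32)] = sqrt(1.125) = 1.06, so about 6% wider
- For the attrition rate itself, at 20%, the approximate 95% half-width is 1.96 x sqrt(0.2 x 0.8 / n): 13.9 percentage points with n = 32 and 12.4 with n = 40

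**The 2-year sentence.** If it describes 24 months of accrual, 10 x 24 = 240 candidates, 240 x 0.25 = 60 enrolled and 60 x 0.80 = 48 completers. Neither 32 nor 64 follows. If it only says where the figure of 10 per month comes from, nothing conflicts.

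**Decliners expected at 25% enrollment**

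- With 40 enrolled: 160 - 40 = 120
- With 32 enrolled: 32 / 0.25 = 128 approached, and 128 - 32 = 96 decline
- The 32 planned controls are 32/120 = 27% or 32/96 = 33% of that pool

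**The case against.** The strongest defence is that the 20% was used. The figure comes out exactly only if attrition is deducted from 40, so the likely error is one of labelling, with completers called recruits. That stands, and it makes the repair easy. It does not remove the error, because the wrong label appears in both places where the target is stated.

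A second defence is that dropouts are not lost to every analysis. Attrition is itself a feasibility outcome, so dropouts count in its denominator. Mixed models and multiple imputation are planned for the other outcomes. This also stands: 26 is the number of completers, not of analysable patients, and the 12% is the cost if dropouts contribute nothing. These methods do not recover measurements that were never taken.

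Three stronger readings are tempting but not supported.

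- A reader might infer that equal groups contradict 25% enrollment, since 32 of 64 is 50%. That would follow only if 64 were everyone approached, which the text does not say. Thirty-two controls can be drawn from 96 to 120 decliners.
- A reader might say that the trial falls short of its stated precision. The protocol states no power, precision or interval width.
- A reader might conclude that the controls would all come from the early months. No section says that the first 32 decliners are taken.

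The 2-year sentence is ambiguous rather than a proven conflict. The Results section allows about 24 months for recruitment and all measurements. Sixteen months of accrual plus 32 weeks (32 x 7 / 30.4 = 7.4 months) is 23.4 months, which fits.

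**Conclusion.** The point holds as a mislabelled recruitment target. The protocol's inputs give 40 enrolled and 32 completers; the text recruits 32, which gives about 26. The shortfall is 8 enrolled, or about 6 completers, with intervals up to about 12% wider than 32 completers would give. This assumes that all 10 monthly patients form the denominator of the 25% and that attrition is 20% as stated.

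Two smaller points on the control group also stand. The Enrollment and Assessment section uses those who do not take part, without limit, while the abstract and Participants section fix 32; with 96 to 120 decliners expected, these need reconciling. In addition, the 2-week criterion runs from consent, a date that controls under a waiver do not have. A comparable date exists, because the choice to join or decline arises at the visit where the surgeon raises the program.

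Severity is moderate: the primary outcome is feasibility, and no hypothesis test was powered on the number.

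**What to change.** In the abstract and the Participants section, state one of two things:

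- enrol 40 to the program and expect 32 completers, which is what the inputs and the 16-month window give; or
- enrol 32 and expect about 26 completers, with the window shown as about 13 months at 2.5 per month, or the longer window explained.

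Say whether the 2-year sentence is only the source of the monthly volume; if so, move it next to that figure.

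For the controls, either use all eligible decliners or keep 32 and state that they are spread over the whole recruitment window. Apply the 2-week criterion to both groups from the date on which the surgeon offers the program.

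The cost is a wording change. The first option means 8 more program participants than the text now says, within the window already planned. The second needs no extra patients but admits a lower number of completers. Only 2 participants had been enrolled when the article was written, so the target can still be corrected early.

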#### Enrollment and Assessment

Each potential participant will go through an assessment with the surgeon, including height, weight, blood pressure, heart rate, pulmonary function tests, grip strength, and a stair climb test as part of their clinical assessment. The thoracic surgeon will then raise the subject of prehabilitation with patients. At this point, patients will have the choice to participate in the prehabilitation program or not. If the participants do not agree to the study, they will continue with a standard of care. If a participant agrees to participate and provides written informed consent in accordance with the Nova Scotia Health Research Ethics Board, they will be referred to the research team and YMCA for immediate start of a prehabilitation program. Those who do not participate in prehabilitation will be used as a comparison group, through a waiver of consent; only those as part of the circle of care will pull these deidentified data for the research team.

#### Intervention

Participants will first have an appointment with a community-based, qualified exercise professional to discuss a tailored prehabilitation program. This will be dependent on a current functional fitness assessment (completed by the surgeon), goals of care, and surgery date. Participants will receive a handbook that will guide them through this process. The handbook will include a calendar of events, a guide to prehabilitation modalities (eg, movement, nutrition, sleep hygiene, stress management, and smoking cessation), publicly available resources (eg, Canada’s Food Guide, CSEP 24-Hour Movement Guidelines, and Smoking Cessation guidelines), and helpful worksheets and other resources (Tobacco Free Nova Scotia Quit Line and mindfulness webinars). Participants will have the choice of delivery modality: either at home, virtual via Zoom (Zoom Video Communications), or at the nearest community-based YMCA. Both in-person and virtual programs will run in the same fashion. All participants will be given 2 resistance bands to assist with their at-home exercises. The intervention will last a total of approximately 8 weeks (Figure 2), depending on the time of surgery and postoperative follow-up. The intervention follows a tailored design, whereby the first 2-3 weeks provide more support, followed by weekly support and then biweekly support. This approach will help contribute to the autonomy of each patient. Following each counseling session, participants will engage in tailored movement sessions.

**Figure 2 figure2:**
[figure not shown]
Timeline of prehabilitation intervention. Note that the “Prehab” phase may be longer than 1-2 weeks depending on the time from diagnosis to surgery. Prehab: prehabilitation.

#### Health Coaching

Participants will work with a qualified exercise professional who is trained in motivational interviewing (MI) to promote positive lifestyle habits. Participants will meet virtually or in person for counseling and movement sessions. Participants will receive 6 health coaching sessions prior to surgery (approximately 3×/week), with 5 additional wellness sessions after surgery (1×/weekly in the first month), and a follow-up (approximately 4-6 weeks after surgery). Health coaching will last 10-15 minutes, and the aim of these MI-informed behavioral counseling sessions is to develop personalized goals. Through MI techniques, qualified exercise professionals will use a shared decision-making approach with participants to promote evidence-based lifestyle modification, while using publicly available, evidence-informed resources to educate the participant on healthy and positive lifestyle behaviors. Following health coaching, the coach will lead the participant through a 15-45-minute movement routine. The booster sessions will provide health coaching over the phone or via Zoom only (Table 1).

**Table 1 table1:** Overview of health coaching sessions.

Session		Week		Topic		Goal of session

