#### Movement Programming

All movement programming will be tailored to each individual participant’s current health status, goals, interests, and abilities. Each one-on-one movement session is expected to last 15-45 minutes and will include time for both warmup and cooldown. Participants will be instructed to begin at a light-to-moderate intensity (ie, 3-6 on a 10-point Borg Scale); systematically progress (ie, periodized); and combine aerobic and resistance training programs for 15-45 minutes, 3 days/week. Should a participant feel that any movement is beyond their comfort level or ability, they will be instructed to inform the qualified exercise professional so that the movement can be modified to better suit their needs (Table 2).

**Table 2 table2:** Outline of a movement programming^a^.

	Description	Frequency	Intensity	Type	Time
Warmup	All sessions begin with a 5-minute warmup to gently increase heart rate and mobilize major muscle groups (RPE^b^ 1-3/10).	—^c^	—	—	—
Aerobic	—	3-7× per week (3 supervised and 0-4 unsupervised)	MICT^d^ (3-6 RPE) or HIIT^e^ (7-9/10 RPE)	Rhythmic repetitive movements (eg, walking, marching, cycling)	10-15 minutes
Resistance	—	3× per week	4-7/10 RPE	Targeting major muscle groups including: Legs (eg, sit to stand) Back (eg, horizontal row) Chest (eg, wall pushups) Core (eg, dead bug) Shoulders or arms (eg, shoulder press or bicep curl)	2 sets of 6-15 reps; 10-15 minutes
Balance	—	3-7× per week (3 supervised and 0-4 unsupervised)	4-7/10 RPE	Examples include single leg balance and tandem stance	2 × 30 seconds; 5 minutes
Flexibility	—	3-7× per week (3 supervised and 0-4 unsupervised)	4-7/10 RPE	Examples include hip flexor or quad stretch, hamstring stretch, and chest openers	2 × 20 seconds; 5 minutes
Locoregional	—	3-7× per week (3 supervised and 0-4 unsupervised)	4-7/10 RPE	Surgery-specific resistance and flexibility exercises (eg, swallowing exercises for esophageal participants)	2 × 20 seconds; 3-5 minutes
Cooldown	All sessions will conclude with a 5-minute cooldown to gently return heart rate to resting values (RPE 1-3/10).	—	—	—	—
Progression—aerobic	Sessions will begin at the lower limit of the desired range (eg, 3 sessions at 40% HRR^f^) and progress to the upper limit of the desired range (eg, 7 sessions at 70% HRR) as tolerated.	—	—	—	—

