#### Qualified Exercise Professional Training

Multiple YMCA-qualified exercise professionals will be trained in health coaching and MI to complete this study. This training will include (1) Thrive health services exercise oncology training [21], an exercise oncology-specific asynchronistic training module; (2) Health Coaching Certification [21], an evidence-based training that focuses on empowering health behavior change; and (3) completion of a full-day workshop on study protocol and MI techniques, including talks from experts in the field, individuals with lived experience of lung or esophageal cancer, and other health care professionals. Each counseling session will have a checklist and protocol for qualified exercise professionals to use outlining the targets and goals for each session. All qualified exercise professionals will be overseen by the YMCA clinical exercise physiologist who will offer advice and guidance on movement programming and health coaching sessions.

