### Statistical Analyses

The statistical analysis for this trial will be conducted with R (R Foundation for Statistical Computing). Participant characteristics will be summarized using descriptive statistics (mean, SD, frequency, and percentage). We will report on reasons for exclusion, attrition, and adverse events with frequency and percentages for each group. Safety will be determined by examining the total number of adverse events that occur over the duration of the program. Adherence to movement sessions will be summarized as a percentage (the number of movement sessions attended divided by the number of available movement sessions).

Baseline demographic and disease-related variables will be compared between prehabilitation and data-only participants using 1-way ANOVA for continuous variables and a chi-square test for categorical variables. The effectiveness analysis will include a linear mixed model to assess the difference in physical fitness and PROs from baseline (T0) to the preoperative (T1), postoperative (T2), 4-6 weeks postoperative (T3), and 32-week long-term follow-up (PROs only) time points, where the time point is the fixed effect and the individual participant is the random effect. A sensitivity analysis will be performed adjusting for sex, surgical type, and age. Linear mixed effect models will also be used to determine between-group differences. An α of .05 will be considered statistically significant. Point estimates and 95% CIs will be calculated for changes in the physical function and PROs at each timepoint and will also be used to provide important information for future sample size calculations. A Poisson regression will be used to estimate differences between groups for postoperative outcomes (ie, length of hospital stays, postoperative complications, return to emergency department, and mortality). Missing outcome data will be imputed using multiple imputation effects. Conclusions will be drawn using comparisons of each time point relative to the baseline.

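### Coaches treat patients one-on-one in the program group only, yet no model allows for coach, so the intervals can be too narrow if coaches share patients and differ in results

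*Protocol article*

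**What the plan says.** **Delivery.** Health Coaching states: "Participants will work with a qualified exercise professional who is trained in motivational interviewing (MI) to promote positive lifestyle habits". The same section has the coach lead the movement routine after the counseling. Movement Programming describes individual, tailored delivery: "Each one-on-one movement session is expected to last 15-45 minutes and will include time for both warmup and cooldown". Qualified Exercise Professional Training says: "Multiple YMCA-qualified exercise professionals will be trained in health coaching and MI to complete this study". It does not say how many, how patients are allocated to them, or whether a patient keeps the same one. Enrollment and Assessment makes the decliners the comparison group, under usual care and so without a coach.

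**Analysis.** Statistical Analyses describes a linear mixed model for change from baseline, "where the time point is the fixed effect and the individual participant is the random effect". Mixed models are then also to be used for between-group differences, with no random effects restated. Postoperative outcomes are compared by Poisson regression, with no clustering term mentioned. The sensitivity analysis adjusts for sex, surgical type and age. The test level is fixed: "An α of .05 will be considered statistically significant". Point estimates and 95% intervals for changes in physical function and patient-reported outcomes are also meant to inform later sample size calculations. Coach appears nowhere in the analysis or in Table 3.

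**The concern.** Two patients guided by the same coach may have more similar outcomes than two patients with different coaches, because the coach chooses content, intensity and progression. This source of correlation exists in one group only, so the design is partially nested. A participant random effect handles repeated measurements within a patient. It treats different patients as independent and cannot absorb a shared coach.

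If coaches do differ, the variance of the program-group mean contains a between-coach part that the stated models leave out. Intervals would then be too short, and tests at the .05 level would reject too often. A later trial sized from these intervals could carry the omission forward. If the coach is not recorded, the pilot could not give even a rough idea of that variance.

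**Working it through.** **1. The plan's own figure.** Participants gives the inputs: "Based on a monthly surgical volume of 10 patients per month to the referring surgeon", and "assuming an enrollment rate of 25% while accounting for 20% attrition within a 16-month recruitment window". Then 10 × 16 × 0.25 = 40 enrolled, and 40 × (1 − 0.20) = 32. The program-group target of 32 reproduces exactly. It is an accrual figure that involves no power, effect size, standard deviation or ICC, so coach clustering does not make it wrong.

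**2. Inputs for the clustering check.**
- From the article: 32 per group, α = .05 (taken as two-sided, in line with the 95% intervals), and coaches in the program group only.
- Assumed, because the article does not give them: k = 2 to 16 coaches with equal caseloads m = 32/k, one coach per patient throughout, equal variances in the two groups, and ICC 0.01 to 0.10.

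**3. Formulas, for one continuous outcome at one time point.**
- Program-group design effect: DE = 1 + (m − 1) × ICC.
- True over naive standard error of the group difference: r = √((DE + 1)/2), because only one of two equal groups is clustered.
- Actual type I error: 2 × (1 − Φ(1.96/r)). Actual coverage is one minus this.

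**4. Worked case, 4 coaches and ICC 0.05.** m = 8. DE = 1 + 7 × 0.05 = 1.35. r = √(2.35/2) = 1.084. Type I error = 2 × (1 − Φ(1.96/1.084)) = 7.1%. Coverage is 92.9%.

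**5. Range.** Each cell gives the increase in the between-group standard error, then the actual coverage of a nominal 95% interval.

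| Coaches (patients each) | ICC 0.01 | ICC 0.05 | ICC 0.10 |
|---|---|---|---|
| 2 (16) | 3.7%; 94.1% | 17.3%; 90.5% | 32.3%; 86.2% |
| 4 (8) | 1.7%; 94.6% | 8.4%; 92.9% | 16.2%; 90.8% |
| 8 (4) | 0.7%; 94.8% | 3.7%; 94.1% | 7.2%; 93.2% |
| 16 (2) | 0.2%; 94.9% | 1.2%; 94.7% | 2.5%; 94.4% |

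At ICC 0 there is no effect. A simulation of a two-sample t interval with 40,000 replicates agrees: coverage 93.0% (4 coaches, ICC 0.05), 90.4% (2 coaches, ICC 0.05) and 86.0% (2 coaches, ICC 0.10).

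**6. Change within the program group.** Here no unclustered comparison group dilutes the effect, so the ratio is √DE. With 4 coaches and an ICC of 0.05 on the change, √1.35 = 1.162: the standard error should be about 16% larger, and coverage is about 91%.

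**7. Could the pilot estimate the coach variance?** In a one-way analysis of variance, the estimate is zero or negative when F < 1. Its probability is P(F(k−1, 32−k) < (1 − ICC)/DE). At ICC 0.05 this is 53% for 2 coaches (threshold 0.95/1.75), 44% for 4 (0.95/1.35) and 42% for 8 (0.95/1.15). A fitted coach variance of zero would therefore say little.

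**The case against.** The strongest case against has five parts.

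- **Silence in a condensed article.** Random-effects structure and provider identifiers are often left to an analysis plan, and none is shown. This has force. However, the article does name a random effect, and the one it names cannot represent a shared coach.
- **The wording belongs to another model.** The participant random effect is stated for change over time. A reader might infer that the between-group model is specified with the participant alone. The text does not say so; carrying it over is the natural reading, no more. The change-over-time model is itself exposed (step 6), so the point does not depend on the carry-over.
- **Nesting is inferred.** A reader might infer a small, fixed set of coaches with one per patient. The article says only that there are multiple coaches. If patients move between coaches, the formula in step 3 does not apply as written. Common training, session checklists and oversight by one exercise physiologist would also tend to reduce differences between coaches. All of this stands, and it is why the size is conditional.
- **The effect may be negligible.** With 4 or more coaches and ICC 0.01 the standard error changes by less than 2%. The 32% figure needs both 2 coaches and ICC 0.10. Nor does the article give any basis for assuming the same ICC for mortality, length of stay or emergency visits. This stands.
- **Limited consequence.** The comparison is secondary, in a nonrandomized pilot whose limitations section already concedes reduced internal validity. This stands and keeps the priority low. It does not remove the value of a nearly free safeguard when the estimates are meant to plan another trial.

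**Conclusion.** The concern holds in conditional form. Coaching is individual and confined to the program group, several coaches deliver it, and the stated analysis has no place for coach. If coaches see several patients each and the coach ICC is positive, the between-group intervals and the program-group change intervals can be too narrow.

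Under the stated assumptions, the understatement of the between-group standard error runs from 0.7% to 32% for 2 to 8 coaches and ICC 0.01 to 0.10. It is 8% in the middle case, with type I error about 7% instead of 5%. These figures are for a continuous outcome at one time point. The mechanism also applies to the Poisson regression, but the figures do not transfer directly.

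The documents do not support the stronger conclusion that the intervals are in fact too narrow, because the number of coaches, the caseloads and the ICC are all unknown. The feasibility primary outcome and the target of 32 are untouched. This is a cheap improvement and does not correct a wrong figure.

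**What to change.** 1. Record the main coach, and any change of coach, for each program participant. The article reports only 2 participants in the program so far, so this can be complete for almost everyone.
2. As a prespecified sensitivity analysis, refit the between-group mixed and Poisson models with a coach random effect in the program group only.
3. Do not rely on the estimated coach variance alone, since it will often be zero. Also show the intervals inflated over a stated range of ICCs, for example 0.01 to 0.10, using the observed caseloads.
4. Present the estimates intended for future sample sizes together with that range.

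The cost is one identifier per program participant, one additional analysis and a few lines of text. The downside is somewhat wider intervals and an imprecise coach variance. The intervention, the recruitment target and the primary outcome do not change.
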